#### Mechanism research

Changes in brain plasticity in different periods before and after rehabilitation intervention will be determined by functional electroencephalogram (EEG) and magnetic resonance imaging (fMRI).

##### Electrophysiological recordings

The NeuroScan ERP recording system (Neuro Scan, Sterling, VA, USA) will be used to record the EEG data of 64 scalp elastic caps, which are expanded according to the international 10–20 system [59]. During the EEG recording, each electrode is referenced to the left mastoid. When recording online, the scalp resistance of each electrode is kept below 10 kΩ. The filtered wideband for recording is 0.05–100 Hz. EEG will be continuously sampled at a frequency of 500 Hz.

##### fMRI protocol

MR Data Acquisition Brain imaging is performed using an optimised protocol, using the 3.0-T MRI scanner (GE pioneer) [60]. The acquisition parameters for functional data are as follows: TR = 2000 ms; TE = 21 ms; FA = 90°; FOV = 240 × 240 mm; matrix = 64 × 64; slice thickness = 4.0 mm; and voxel size = 3.75 × 3.75 × 4.0 mm. During the Rs-fMRI scan, participants are instructed to relax with their eyes closed, but to not fall asleep. T1-weighted structural images are acquired using a three-dimensional magnetisation prepared rapid acquisition gradient-echo sequence (TR = 2530 ms, TE = 2.93 ms, FA = 7°, FOV = 256 mm, a 256 × 256 matrix, and a slice thickness of 1.0 mm) [61].

### Data collection

At baseline, the following data will be collected: gender, age, occupation, education level, current medication status, detailed physical and neurological examinations. Inclusion and exclusion criteria will be evaluated. MDS-UPDRS III will be evaluated at T0 and T1. The PDQ-39 will be evaluated at 4 weeks, 12 weeks and 24 weeks after intervention. NMSS will be assessed at T0, T1, T2, T3 and T4. The 6MWD, 10MT, TUG, BBS, MRI and EEG will be scanned at T0 and T1. All the above assessments are evaluated blindly by the raters, who are unaware of the treatment methods used by the patients (Figs. 2 and 4).

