**Methods:**

This randomised, double-blind clinical trial will enrol 50 Parkinson’s disease patients aged 45–70 years with Hoehn and Yahr scale scores of 1–3. Patients are randomly assigned to either the iTBS + physiotherapy or sham-iTBS + physiotherapy group. The trial consists of a 2-week double-blind treatment period and a 24-week follow-up period. iTBS and sham-iTBS will be administered twice daily for 10 days based on physiotherapy. The primary outcome will be the third part of Movement Disorders–Unified Parkinson’s Disease Rating Scale (MDS-UPDRS III) from the baseline to the first 2 days following completion hospitalised intervention. The secondary outcome will be 39-item Parkinson’s Disease Questionnaire (PDQ-39) at 4 weeks, 12 weeks and 24 weeks after intervention. Tertiary outcomes are clinical evaluations and mechanism study outcomes such as NMSS, 6MWD, 10MT, TUG, BBS, MRI, and EEG, the length of time between the drug needs to be adjusted when symptoms fluctuate.

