### Follow-up

Treatment outcomes will be estimated at baseline (week 0) and after intervention for 2 days (T1), 4 weeks (T2), 12 weeks (T3) and 24 weeks (T4). We will call each participant to keep in contact and remind them of the next interview to avoid being lost to follow-up.

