### Secondary outcome

The secondary outcomes measures were minimal clinically meaningful response (− 4.72) on 39-item Parkinson’s disease questionnaire (PDQ-39) at 4 weeks, 12 weeks, and 24 weeks after intervention [51]. The PDQ-39 is designed to assess the quality of life of people with PD and consists of 39 programmes which are divided into eight core issues: communication, social support, disease stigma, mobility, emotional health, ability to perform daily living, cognition and physical discomfort. Patients are required to indicate the frequency of each corresponding event in the previous month. The final results of the scale include one global index score, eight sub core scores and a weighted percentage of problem severity. Comparative studies of other quality of life (QoL) scales have shown that PDQ-39 has the highest sensitivity to QoL evaluation in patients with PD, as it presents a higher Cronbach’s alpha index (0.76–0.93) regarding the correlation of the emotional changes of the people with PD with their status of health [52]. This concludes with the necessity of similar highly confident reliability use of the appropriate evaluation scales between clinical trials.

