**Fig. 4 Fig4:**
[figure not shown]
Time schedule of enrolment, interventions and assessments. At baseline (T0), subjects will receive and sign informed consent, and general patient information will be collected. The MDS-UPDRS III will be used to comprehensively evaluate MS of PWP at T0 and T1. The PDQ-39 evaluates the quality of life of patients with PD (PWP) at 4 weeks, 12 weeks and 24 weeks after intervention. The NMSS allows quantitative evaluation of NMS of PD. The changes in brain plasticity in different periods before and after rehabilitation intervention (at T0 and T1) were determined by magnetic resonance imaging (fMRI) and electroencephalogram (EEG). The 6-min walk distance (6MWD), 10-m walk (10MT), TUG, BBS, FTSTS for balance and posture control, and walking ability will be evaluated at T0 and T1. Any AEs will be recorded during the research. Safety indices will also be tested at T0 and T1. AEs will be recorded during the research

Safety indices such as blood routine, urine routine, stool routine, liver and kidney function, and electrocardiogram will also be tested at T0 and T1. Adverse events will be recorded during the research. On the consent form, participants will be asked if they agree to use of their data should they choose to withdraw from the trial. Participants will also be asked for permission for the research team to share relevant data with people from the Universities taking part in the research or from regulatory authorities, where relevant. With patient consent, biological samples such as blood, urine, faeces and saliva will be collected at T0 and T1 for molecular biological analysis. Before the start of the study, investigators will receive standardised training on the data collection strategy and guidelines for the different scales used to assess outcomes. During the trial, data will be collected by trained researchers to prevent bias. If the subjects experience the “on–off” phenomenon, the data collection should be conducted during the “on” period. All treatments and evaluations will be conducted at the same period after levodopa taken before and after the intervention to limit the effects of drug fluctuations.

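### The only secondary endpoint, a PDQ-39 response of −4.72 points, needs a baseline score, but the written PDQ-39 schedule has no baseline visit and conflicts with the Follow-up section

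*Protocol article*

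**What the plan says.** The Secondary outcome section defines one endpoint: "The secondary outcomes measures were minimal clinically meaningful response", with −4.72 as the threshold on PDQ-39, judged "at 4 weeks, 12 weeks, and 24 weeks after intervention". No other measure stands under that heading, and the Abstract likewise names PDQ-39 alone as the secondary outcome.

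Four places give times for PDQ-39, and they agree:

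- Abstract, Methods: "PDQ-39) at 4 weeks, 12 weeks and 24 weeks after intervention"
- Secondary outcome: the three visits quoted above
- Data collection: "The PDQ-39 will be evaluated at 4 weeks, 12 weeks and 24 weeks after intervention"
- Fig. 4 legend: "The PDQ-39 evaluates the quality of life of patients with PD (PWP) at 4 weeks, 12 weeks and 24 weeks after intervention"

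The Data collection section opens with its baseline items: "At baseline, the following data will be collected: gender, age, occupation, education level, current medication status, detailed physical and neurological examinations". PDQ-39 is not among them.

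The Follow-up section contains the one contrary statement: "Treatment outcomes will be estimated at baseline (week 0) and after intervention for 2 days (T1", followed by the 4-, 12- and 24-week visits. It names no instrument.

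**The concern.** A response threshold of −4.72 cannot be applied to a single score. PDQ-39 is built from how often problems occurred, so a negative value makes sense only as a change. For that change to reflect treatment, the reference score must come from before treatment. The visits listed for PDQ-39 all come after treatment, the first of them four weeks after it ends.

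The Discussion paragraph of the Abstract rests a possible first-line recommendation on improvement in both quality of life and motor function. As the endpoint is defined, the quality-of-life half depends on a score that the schedule does not collect. An analysis plan cannot repair this later, because no analysis rule creates a baseline that was never measured. Last observation carried forward, the missing-data rule in the Statistical analysis section, moves values forward in time and cannot supply an earlier one.

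Timing matters too. According to Trial status, the first patient entered in April 2022 and recruitment is ongoing. The scale asks about the previous month, so a baseline that was not taken at entry is lost for that patient.

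**Working it through.** The article gives no sample size or power for PDQ-39, so there is no stated figure to reproduce for this endpoint. The check compares what the endpoint needs with what is scheduled.

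**Step 1: what the endpoint needs.** Response at visit t means PDQ-39(t) − PDQ-39(T0) ≤ −4.72, for t = T2, T3 and T4 (4, 12 and 24 weeks). This needs T0 and each of T2, T3 and T4.

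**Step 2: what is scheduled, instrument by instrument.**

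| Instrument | Times given | T0 named? | Source |
|---|---|---|---|
| MDS-UPDRS III | T0, T1 | yes | Data collection; Fig. 4 legend |
| NMSS | T0 to T4 | yes | Data collection |
| 6MWD, 10MT, TUG, BBS | T0, T1 | yes | Data collection; Fig. 4 legend |
| MRI, EEG | T0, T1 | yes | Data collection; Fig. 4 legend |
| FTSTS | T0, T1 | yes | Fig. 4 legend |
| PDQ-39 | 4, 12, 24 weeks | no | Abstract; Secondary outcome; Data collection; Fig. 4 legend |

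NMSS is the closest comparator, because it is also followed to 24 weeks. For it the article writes "NMSS will be assessed at T0, T1, T2, T3 and T4". PDQ-39 is the only outcome instrument in these schedules that has times but no T0.

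**Step 3: does the Follow-up sentence fill the gap?** Taken as a schedule for every outcome, it would put MDS-UPDRS III at T2, T3 and T4, and MRI and EEG there as well. Data collection gives all three only T0 and T1. The sentence therefore works as a list of study visits, not as a schedule for each instrument. It contradicts the specific passages without overriding them.

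**Step 4: consequence, conditional on following the instrument-level schedule.**

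- Patients with a T0 score: 0 of 50.
- Evaluable responder assessments: 0 of 50 × 3 = 150.
- With T0 added for everyone: up to 50 patients, or 50 × (1 − 0.12) = 44 at the 12% dropout allowed for in the Sample size section. That rate was set for the primary outcome and may not hold at 24 weeks.

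**Step 5: what is not affected.** The primary outcome has T0 and T1, and its sample size is independent of PDQ-39. With δ = 4.89, σ = 4.88, 90% power and two-sided 0.05 (the article does not state the sidedness), n = (1.960 + 1.282)² × 2 × 4.88² / 4.89² = 20.93, which rounds up to the stated 21 per group.

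**The case against.** The strongest reply is that the documents do not show that the baseline is missing in practice.

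- The Follow-up section says outcomes are estimated at baseline, and on its face that covers the named secondary outcome.
- The schedules are imperfect, so silence in them is weak evidence. Data collection omits FTSTS, which the Fig. 4 legend places at T0 and T1. The legend gives no times for NMSS.
- The PDQ-39 sentences repeat the endpoint wording, while the instruments around them carry T-codes. The endpoint times may simply have been copied into the schedule.
- The Fig. 4 grid is not shown, and the article condenses a fuller protocol.

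This stands as a limit on certainty. A reader might infer that no enrolled patient has a baseline PDQ-39. The text does not support that, and the loss in Step 4 holds only if the written schedule is what sites follow. The reply does not remove the defect, though. Four places give explicit times that do not fit the endpoint, and the one general sentence in the other direction cannot be read literally. These are stated times, not detail left to a fuller document.

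A second reply is that quality of life can still be tested. The Abstract gives PDQ-39 at three times with no threshold, and randomisation makes a between-arm comparison of post-treatment scores valid without a baseline. That is correct, so a reader should not infer that the trial can say nothing about quality of life. What fails is the responder endpoint as the Secondary outcome section defines it.

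A reader might also want to size the problem by the precision lost without baseline adjustment. The usual factor, 1/(1 − ρ²), applies to a continuous score, whereas the stated endpoint is binary. The article gives no baseline-to-follow-up correlation either. No such multiplier is used here.

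**Conclusion.** The point holds as a defect in the written plan. The sole secondary endpoint requires a pre-treatment PDQ-39 score, every passage that times PDQ-39 leaves it out, and the general Follow-up statement conflicts with those passages. If the instrument-level schedule is followed, responder status is undefined for all 50 planned patients at all three visits. What would remain is a valid comparison of post-treatment scores, which is less precise than a baseline-adjusted one to the extent that baseline predicts follow-up, and which is a different endpoint from the one stated.

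The conclusion rests on reading −4.72 as a patient-level change from before treatment, and its size rests on the written schedule being applied. It does not establish that baseline scores are absent. The contradiction between sections is certain; the loss of data is conditional. Correction is needed either way, and promptly, because any loss grows with each patient who enters without a T0 score. The primary outcome and its sample size are untouched.

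**What to change.** 1. Establish whether PDQ-39 is already collected at T0. If it is, correct the Secondary outcome section, the Data collection section and Fig. 4 to say so. If it is not, add it in those three places for every patient still to enter, at T0 and before the first stimulation.
2. Define response in the Secondary outcome section as a change from T0 of −4.72 or lower at 4, 12 and 24 weeks.
3. Reword the Follow-up sentence so that it lists visits and refers to Data collection for the instruments measured at each.
4. Report how many enrolled patients lack a T0 score. Keep their post-treatment scores in a longitudinal model that treats baseline as one of the outcomes, with a common mean across arms, as randomisation justifies. Do not impute their responder status. Restrict the responder analysis to patients with a T0 score and say so.

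The cost is one 39-item questionnaire at a two-day baseline visit that already exists, plus an amendment, which the Data monitoring section says needs ethics approval. The part that cannot be bought back is any baseline already missed: the amendment helps only later entrants, and the responder analysis would be smaller by the number enrolled without T0.

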**Fig. 4 Fig4:**
[figure not shown]
Time schedule of enrolment, interventions and assessments. At baseline (T0), subjects will receive and sign informed consent, and general patient information will be collected. The MDS-UPDRS III will be used to comprehensively evaluate MS of PWP at T0 and T1. The PDQ-39 evaluates the quality of life of patients with PD (PWP) at 4 weeks, 12 weeks and 24 weeks after intervention. The NMSS allows quantitative evaluation of NMS of PD. The changes in brain plasticity in different periods before and after rehabilitation intervention (at T0 and T1) were determined by magnetic resonance imaging (fMRI) and electroencephalogram (EEG). The 6-min walk distance (6MWD), 10-m walk (10MT), TUG, BBS, FTSTS for balance and posture control, and walking ability will be evaluated at T0 and T1. Any AEs will be recorded during the research. Safety indices will also be tested at T0 and T1. AEs will be recorded during the research

Safety indices such as blood routine, urine routine, stool routine, liver and kidney function, and electrocardiogram will also be tested at T0 and T1. Adverse events will be recorded during the research. On the consent form, participants will be asked if they agree to use of their data should they choose to withdraw from the trial. Participants will also be asked for permission for the research team to share relevant data with people from the Universities taking part in the research or from regulatory authorities, where relevant. With patient consent, biological samples such as blood, urine, faeces and saliva will be collected at T0 and T1 for molecular biological analysis. Before the start of the study, investigators will receive standardised training on the data collection strategy and guidelines for the different scales used to assess outcomes. During the trial, data will be collected by trained researchers to prevent bias. If the subjects experience the “on–off” phenomenon, the data collection should be conducted during the “on” period. All treatments and evaluations will be conducted at the same period after levodopa taken before and after the intervention to limit the effects of drug fluctuations.

### Data management

An EDC system that relies on the clinical research data platform of the Parkinson Medical Center, Beijing Rehabilitation Hospital will be used for data entry and management [61]. The data entry will be carried out by data collectors. Participant information will be stored in the EDC system, which investigators can access using a password. The completeness of case report forms and consistency between the code and the subject’s screening entry list will be verified. Data will be validated after entry into the EDC system, and the original case will be reviewed based on these results. Final data will be exported as an Excel (Microsoft, Redmond, WA, USA) spreadsheet. [name] and [name] will conduct an interim analysis and make a final decision on whether to suspend the trial based on the interim results. [name] will have access to the final trial dataset, and only authorised researchers can access the data.

### Data monitoring

We have already established an independent data and safety monitoring board (DSMB) for this study that is independent of the sponsor, consisting of a rehabilitation physician specialist, a neurologist and a statistician. The DSMB will oversee whether the trial follows the study design and standard guidelines. The neurologist will assess, manage and classify all adverse events (AEs). All serious AEs (SAEs) will need to be reported to the main researchers, the ethics committees and the DSMB, within 24 h of occurrence. The DSMB and the main researchers will discuss such issues. The ethics committees and the DSMB will have the right to terminate the trial if they deem that such action is appropriate. The role of the statistician is to review the safety data. The DSMB meet to review trial conduct every 3 months. The DSMB meet to review conduct throughout the trial period. The DSMB is also responsible for monitoring the timeliness, completeness and accuracy of data, and urging researchers to improve data reporting and correction in a timely manner. DSMB members are independent of the sponsor and have no competing interests. There is also a coordinating centre that running the trial day-to-day and providing organisational support every day.

Any amendment to the protocol will require approval by the ethics committee before implementation. Participant personal information will be kept private; only relevant codes will be used during statistical analysis. Participant information will be stored in the EDC system at the Beijing Rehabilitation Hospital, Capital Medical University, China, for 5 years. The final dataset will be available to the principal investigator and independent statistician. The results of this study will be published in a peer-reviewed journal and presented at national and international conferences.

### Sample size

This is a randomised, double-blind, parallel, placebo-controlled clinical trial assessing the efficacy of iTBS among patients with PD. We used the primary outcome MDS-UPDRS III and considered that a plausible effect of the intervention would be a change in MDS-UPDRS III of − 4.89 points (− 3.25 points is for detecting minimal clinically important improvement difference on the Motor Examination part of MDS-UPDRS [62]). Values of mean (SD) for MDS-UPDRS III in control group will be 4.88 [63].

Based on a 1:1 ratio of patients in the iTBS + PT and Sham-iTBS + PT groups, the minimum sample size was calculated with formula shown in Eq. (1), providing 90% power with a level of 0.05.1$$n= \frac{{{(Z}_{a}+ {Z}_{\beta })}^{2} \times 2{\sigma }^{2}}{{\delta }^{2}}$$

In Eq. (1), *n* represents the sample size of each group, *σ* represents the values of mean (SD) for MDS-UPDRS III in the control group, *δ* represents the difference between the mean of the iTBS + PT group and the Sham-iTBS + PT group; *α* represents type 1 errors and *β* represents type 2 errors.

Application of Eq. (1) showed that 21 are required for the iTBS + PT group and the Sham-iTBS + PT group, respectively. Considering a 12% dropout rate, we plan to recruit 50 cases for the two groups.

### Statistical analysis

SPSS v22.0 software (SPSS Inc., Chicago, IL, USA) will be used for data processing and analysis. Measurement data are expressed as mean ± standard deviation. The intention-to-treat (ITT) analysis will be the primary analysis of this study, and per-protocol(PP) analysis will be a secondary analysis if there are patients that did not receive the intervention because of problems of the intervention itself: adverse effects, difficult administration or adherence, etc. The missing data will be processed using the last observation carried forward (LOCF).The sensitivity analyses will be used if there are unbalanced losses to follow up or if too many losses, etc. The significance level for each test will be set at *P* < 0.05.

MRI pre-processing will be carried out using the data processing assistant for Rs-fMRI, which runs with the statistical parametric mapping software (SPM82) [64]. After the EEG data is recorded, it is processed offline through MATLAB software scripts and the EEGLAB toolbox [64].

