### Primary outcome measures

The primary outcome will be the change in the third part of Movement Disorders–Unified Parkinson’s Disease Rating Scale (MDS-UPDRS III) from the baseline to the first 2 days following completion hospitalised intervention. MDS-UPDRS III [50] contains 18 items and each item was rated 0 to 4 points. The higher the scores, the poorer the motor symptoms (MS).

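### MDS-UPDRS III is measured only at T0 and T1, so LOCF scores every patient missing T1 as no change; if the whole 12% dropout falls before T1, power at 25 per arm drops to about 88%

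*Protocol article*

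**What the plan says.** Under Primary outcome measures, the endpoint is the change in MDS-UPDRS III "from the baseline to the first 2 days following completion hospitalised intervention". Data collection fixes its timing: "MDS-UPDRS III will be evaluated at T0 and T1". There is one post-baseline value and nothing in between.

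Under Statistical analysis, "The intention-to-treat (ITT) analysis will be the primary analysis of this study", and for gaps, "The missing data will be processed using the last observation carried forward (LOCF". The rule is general. The same paragraph adds: "The sensitivity analyses will be used if there are unbalanced losses to follow up or if too many losses". It gives no threshold and names no method.

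Under Sample size, the assumed effect is "a change in MDS-UPDRS III of − 4.89 points", and the spread is given as "Values of mean (SD) for MDS-UPDRS III in control group will be 4.88". The formula gives 21 per arm for 90% power at 0.05, followed by: "Considering a 12% dropout rate, we plan to recruit 50 cases for the two groups". The Dropping criteria include patients who do not complete the training, so some loss before T1 is foreseen.

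The secondary outcome is a responder measure: reaching a PDQ-39 improvement of 4.72 at 4, 12 and 24 weeks.

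**The concern.** LOCF needs an earlier post-baseline value to carry. For MDS-UPDRS III there is none, so the rule amounts to carrying the baseline forward: a patient with no T1 score is recorded as not having changed. That is not a neutral value here. Both arms get ten days of physiotherapy, which the Background and Discussion describe as effective, so the article's own premise is that a typical patient in either arm improves.

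Two things are at stake. First, the sample size and the analysis treat dropouts differently. The inflation from 21 to 25 per arm makes sense if dropouts leave the analysis, but under ITT with LOCF they stay in as zeros, pulling the difference toward zero and usually adding spread. Second, if the arms lose different numbers of patients before T1, the zeros fall unevenly and the estimated difference moves even when stimulation does nothing.

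For PDQ-39, LOCF would let a patient who responded at 4 or 12 weeks and then left count as a responder at 24 weeks, in a trial that aims to show lasting benefit in a disease it calls progressive.

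**Working it through.** **Inputs.** From Sample size: difference δ = 4.89, σ = 4.88, α = 0.05, power 90%, dropout q = 12%. From Participants: 25 per arm. Assumptions: 4.88 is the SD of the change (the text does not say); the test is two-sided (this reproduces the stated n; one-sided gives 18); the sham arm's mean change μ is not given, so it is varied from 0 to −8.

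**1. The plan's own figure.** n = (1.960 + 1.2816)² × 2 × 4.88² / 4.89² = 20.93, so 21 per arm. This reproduces. Inflating, 21 / 0.88 = 23.9, so 24 per arm or 48 in total; 50 are planned. With 12% removed, 25 × 0.88 = 22 remain per arm.

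**2. Power if dropouts leave the analysis.** Power = Φ(δ / (σ√(2/n)) − 1.96).
- n = 21: 90.1%
- n = 22: Φ(3.323 − 1.960) = 91.4%
- n = 25, no loss: 94.3%

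**3. Power under LOCF, all 12% lost before T1, equal in both arms.** The expected difference is 0.88 × 4.89 = 4.30. With σ held at 4.88 and 25 per arm, the standard error is 4.88 × √(2/25) = 1.380, so power = Φ(4.30/1.380 − 1.96) = Φ(1.158) = 87.6%. About 28 analysed per arm would be needed for 90%.

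**4. Allowing for the spread that the zeros create.** The variance in an arm with mean change m is (1 − q)σ² + q(1 − q)m². For sham μ = −3.25 (active −8.14):
- sham: 0.88 × 23.81 + 0.1056 × 10.56 = 22.07
- active: 0.88 × 23.81 + 0.1056 × 66.26 = 27.95
- SE = √((22.07 + 27.95)/25) = 1.415; power = Φ(4.30/1.415 − 1.96) = 86.0%

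| Assumed sham change | Normal approximation | Simulated t-test, exactly 3 of 25 per arm set to 0 |
|---|---|---|
| 0 | 89.8% | 89.5% |
| −2 | 87.8% | 88.1% |
| −3.25 | 86.0% | 87.2% |
| −5 | 82.7% | 84.7% |
| −8 | 75.3% | 78.4% |

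**5. Break-even loss before T1.** With σ held at 4.88, 90% power needs (1 − q) × 4.89 / 1.380 = 1.960 + 1.2816 = 3.2416, so 1 − q = 0.915 and q = 8.5%. With the step 4 variance, the break-even runs from about 3% (sham −8) to about 11% (sham 0).

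**6. Unequal loss, no true effect (assumed figures).** Let both arms truly change by −5, with T1 missing in 5/25 sham and 1/25 active. The active mean becomes 0.96 × (−5) = −4.8 and the sham mean 0.80 × (−5) = −4.0, a spurious benefit of 0.8 points. Simulated two-sided type I error is about 7.8%, against about 6.2% for a shared change of −3.25.

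**7. Unequal loss, true effect 4.89, sham change −3.25 (assumed).** If 24% are lost in the active arm only: 0.76 × (−8.14) + 3.25 = −2.94. If 24% are lost in the sham arm only: −8.14 + 0.76 × 3.25 = −5.67. The true difference is −4.89, so the bias can run in either direction.

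**The case against.** A reader might infer that every dropout is scored as zero and that 90% power is therefore lost. The article does not support that. Only patients without a T1 value are affected. T1 falls within two days of a ten-day hospital course, while follow-up runs to 24 weeks, and the article does not say when the 12% leave. Anyone lost after T1 has an observed primary outcome. Placing all 12% before T1 is the worst reading of that figure. The plan also has slack, at 94.3% with no loss: in t-test simulations with sham changes from 0 to −5, one missing T1 per arm leaves 91–92%, and two leave 88–91%.

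The yardstick matters too. The stated 90% comes from a normal approximation; by t-test, 21 per arm has 88.7%. On the plan's own method, a sham arm that does not change gives 89.8%, practically no shortfall.

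Nor is the estimate biased whenever someone drops out. With no true effect and equal loss, the difference in means is unbiased; with a true effect and equal loss, it shrinks toward zero. Bias in favour of iTBS requires unequal loss, and the article names imbalance as a trigger for sensitivity analysis, whose details may sit in a fuller plan.

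All of this stands and limits the size of the problem. It does not rescue the rule: where T1 is missing, the main analysis inserts a value that the trial's own rationale contradicts, and a conditional sensitivity analysis leaves that main analysis unchanged.

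**Conclusion.** The point holds, with conditions. LOCF on MDS-UPDRS III is baseline carried forward, and the sample size and analysis sections handle dropouts inconsistently. If the full 12% is lost before T1 and loss is equal, the expected difference is 4.30 instead of 4.89 and power is about 87.6%, or about 90% down to 78% (t-test simulation) for assumed sham changes of 0 to −8. Below roughly 8.5% loss before T1 (SD held at 4.88), the stated 90% is kept. With unequal loss the estimate can be inflated or diluted; the 0.8-point spurious benefit and type I error near 8% illustrate this under assumed figures and are not a forecast. All figures take 4.88 as the SD of the change. The PDQ-39 concern is one of principle; its size was not calculated.

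**What to change.** For MDS-UPDRS III, replace LOCF as the main method with baseline-adjusted ANCOVA on observed T1 values, or the same model with multiple imputation by arm. With a single post-baseline value and 25 per arm, the simpler form is adequate. Keep baseline carried forward only as a sensitivity analysis. Commit to a sensitivity analysis for missing T1 whatever the losses turn out to be.

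For the PDQ-39 responder outcome, do not carry a 4- or 12-week response to 24 weeks as the main analysis. Use a method suited to a repeated binary outcome, or derive response from a repeated-measures model of the score.

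The cost is revised wording in the analysis section and slightly more programming; these changes need no extra data collection. The price in assumptions is that the main analysis then relies on data being missing at random, which the unconditional sensitivity analysis is there to test.
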